### Aims and hypotheses

This study aims to assess the effect of ABCR vs. a control treatment on cognitive improvement in (i) BD patients in full or partial remission and to (ii) assess early neural changes indicative of potential treatment benefits on cognition.

We hypothesize (i) that ABCR vs. a control treatment has a beneficial effect on cognition in patients with BD in full or partial remission (the primary hypothesis of the study). We hypothesize (ii) that this treatment-associated improvement of cognition translates into better functional capacity at the 6-months follow-up assessment (secondary outcome). For the *exploratory* analysis of the neuronal underpinnings of these treatment effects, we hypothesize that ABCR will produce an early change in neural activity in the dorsal prefrontal cortex during working memory and strategic memory encoding in the direction of the prefrontal activity levels seen in a healthy control group (i.e., partial normalization) and this activity will correlate with ABCR-associated improvements in cognitive function.

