### Procedure

Upon their first visit to the Copenhagen Affective Disorder Research Center (CADIC), participants are informed about the project and provide written informed consent after which they undergo an eligibility assessment. The written informed consent will be obtained by the first author. Upon inclusion, participants are randomized with stratification for gender and age (< or ≥ 35 years) to either 10 weeks of ABCR (active treatment) or patient group (control treatment). When 4–6 participants have been randomized to a group, baseline assessments will be carried out in the week prior to the first group session. Deterioration in terms of clinical symptoms at the baseline assessment is recorded, but participants are not excluded if their symptoms worsen. The baseline assessment is completed over two days, 1–3 days apart for practical reasons and to avoid attrition.

On day 1, participants’ mood is rated with the Hamilton Depression Rating Scale and Young Mania Rating Scale, followed by a functional magnetic resonance imaging (fMRI) scan encompassing spatial and verbal working memory N-back tasks, a picture encoding task, a resting state, and a structural scan. On day 2, participants attend the research center in the morning for a fasting blood test. A comprehensive neuropsychological test battery is administered by a treatment-blinded outcome assessor. Participants fill in questionnaires concerning subjective cognitive complaints, psychosocial functioning, and quality of life. Functional capacity is assessed using a clinician-rated interview and a performance-based assessment. Finally, sleep quantity and quality in the past 3 days is assessed.

After 2 weeks of ABCR or control treatment, the fMRI, neuropsychological testing, and an assessment of mood and subjective cognition are repeated to assess whether early task-relevant neural activity changes—prior to improvement on the behavioral measures of cognition—correlate with and predict subsequent cognitive improvement after treatment completion. The neuropsychological assessments and questionnaires, as well as assessments of functional capacity and quality of life, are repeated within 2 weeks after treatment completion (primary outcome assessment time), and 6 months after treatment completion. An intermediate clinical mood rating is performed during week 6.

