#### N-back working memory tasks

fMRI data from the N-back working memory tasks will be analyzed using a region-of-interest analysis to assess differences between the ABCR and control groups in neural activity in the dlPFC after 2 weeks (adjusting for any differences in neural differences at baseline). In addition, we will conduct volume-of-interest analyses of the dorsal prefrontal cortex to examine our hypothesis. Exploratory whole-brain analyses will be conducted to investigate any effects in other brain regions.

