#### Strategic picture encoding

We will conduct volume-of-interest analyses of the dorsal prefrontal cortex and the hippocampi to assess the fMRI data from the strategic picture encoding task. Finally, exploratory whole-brain analyses will be conducted to investigate any effects in other brain regions.

Any differences in neural activity will be correlated with potential changes in the cognitive composite score after 2 weeks of treatment and post-treatment. If there is a significant correlation with cognition at post-treatment, multiple regression analysis will be carried out, adjusting for mood and demographic characteristics, to assess whether early changes in neural activity are predictive of pro-cognitive effects.

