## Discussion

The present study investigates the effect of ABCR on cognitive improvement in clinically stable BD patients. It also explores early treatment effects on dorsal prefrontal activity to examine neurocircuitry target engagement. This will contribute to the broader aim of identifying a neurocircuitry biomarker model for pro-cognitive effects.

All participants are required to present with objective cognitive impairment to be enrolled in the study. The criteria are based on findings from our previous EPO trials, showing that patients with worse objective cognitive functioning at baseline have the greatest chance of achieving treatment efficacy [50] and on the subsequent methodological recommendations for cognition trials in BD by the Targeting Cognition Task Force of the ISBD [44]. The criteria will serve to ensure that the sample is enriched for cognitive impairment, which will enhance the chances of detecting treatment-associated cognitive improvement [9]. However, it could cause a recruitment challenge since it is estimated that 30–70% of euthymic patients with BD show clinically relevant objective cognitive impairment [1–3]. As the study will recruit up to 58 patients with BD in full or partial remission to ensure complete data sets for 52 patients, multiple recruitment channels have been identified: psychiatric centers run by Mental Health Services in the Capital Region of Copenhagen, consultant psychiatrists, advertisements, and the Copenhagen Affective Disorder Clinic in Rigshospitalet. A break will interleave the fifth and sixth session in the ABCR program with sessions occurring twice a week, to ensure that all ABCR participants are assessed with fMRI and neuropsychological tests following 2 weeks (four sessions) of treatment.

There are no known direct risks associated with participation in the study. All participants are covered by public insurance provided by the Patient Compensation Association. The use of a control group, where participants are not offered treatment targeting cognitive impairment, will control for non-specific therapeutic effects of being in a group setting, which may increase participants’ quality of life and functional capacity. The use of a control group is also rendered necessary, as there is currently no effective treatment for cognitive impairment with direct and lasting effects [9].

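### The exploratory regression that is to show early neural change predicts cognitive gain lists mood and demographics as covariates but not the baseline composite, so its coefficient may partly reflect baseline impairment

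*Protocol article*

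**What the plan says.** The analysis is set out in the protocol article under Functional MRI analyses, at the end of Strategic picture encoding. It has two steps.

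- **Gate.** "Any differences in neural activity will be correlated with potential changes in the cognitive composite score after 2 weeks of treatment and post-treatment".
- **Follow-up.** "If there is a significant correlation with cognition at post-treatment", then "multiple regression analysis will be carried out, adjusting for mood and demographic characteristics, to assess whether early changes in neural activity are predictive".

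No covariate other than mood and demographic characteristics is named. The only baseline adjustment in the fMRI sections is in the N-back comparison of the two arms ("adjusting for any differences in neural differences at baseline"). That concerns neural activity, not cognition, and belongs to a different model.

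Three other places bear on the point:

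- Procedure gives the purpose: early neural changes are to "correlate with and predict subsequent cognitive improvement after treatment completion".
- The Discussion, citing the group's earlier erythropoietin (EPO) trials, says that "patients with worse objective cognitive functioning at baseline have the greatest chance of achieving treatment efficacy", and uses this to justify enrolling only impaired patients. On the neural findings it adds: "This will contribute to the broader aim of identifying a neurocircuitry biomarker model for pro-cognitive effects".
- Aims and hypotheses labels the neural analysis exploratory. It expects prefrontal activity to move towards the level of healthy controls.

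**The concern.** A change score is usually correlated with its own baseline, and the Discussion links worse baseline cognition to a better chance of response. If patients who start more impaired also show more change on the scan, as a move towards healthy-control levels makes plausible, baseline cognition lies behind both variables. Neural change and cognitive gain would then correlate even if the scan adds nothing to the baseline test.

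The named covariates are not chosen to remove this. The gate cannot screen it out either, because it is an unadjusted correlation open to the same influence. At stake is what the word predictive would mean in the trial report. A useful biomarker has to add to what the baseline composite already shows without a scan, and the regression as described does not test that.

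**Working it through.** **Inputs.** The Sample size section gives 52 complete data sets, 26 per arm. It gives no figure for this regression, so there is none to reproduce. The documents give no correlation of the baseline composite with its change or with neural change, so the values below are assumptions.

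**Step 1: change against baseline.** With equal variances and pre-post correlation rho, corr(change, baseline) = -sqrt((1 - rho)/2).
- rho = 0.5: -sqrt(0.25) = -0.50
- rho = 0.7: -sqrt(0.15) = -0.39

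**Step 2: no true link given observed baseline.** The correlation induced between neural change and gain is then the product of the two baseline correlations. For 0.5 and 0.4 it is 0.20. By Fisher's z, atanh(0.20) x sqrt(52 - 3) = 0.203 x 7 = 1.42, and P(Z > 1.96 - 1.42) is about 29%. Simulation (20,000 runs per row, n = 52, two-sided 5%) agrees:

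| Baseline with gain (size) | Baseline with neural change (size) | Induced r | Rejection, no baseline composite |
|---|---|---|---|
| 0.39 | 0.3 | 0.12 | 13.3% |
| 0.39 | 0.4 | 0.16 | 20.2% |
| 0.50 | 0.3 | 0.15 | 18.5% |
| 0.50 | 0.4 | 0.20 | 29.9% |

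With the baseline composite in the model, rejection is 4.7 to 5.2%.

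**Step 3: does the stated gate help?** A separate simulation used three independent covariates in place of mood and demographics, with both baseline correlations equal (n = 52):

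| Both correlations | Stated covariates | Gate and stated covariates | Gate and baseline-adjusted |
|---|---|---|---|
| 0.3 | 9.7% | 8.1% | 2.9% |
| 0.4 | 19.9% | 17.8% | 2.6% |
| 0.5 | 41.1% | 38.5% | 2.7% |
| 0.6 | 72.8% | 71.2% | 2.9% |

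The gate barely helps while the regression omits baseline. At n = 26 (one arm) the stated covariates alone give 6.7%, 11.3%, 20.9% and 40.2%. If baseline is unrelated to both variables, rejection is about 5% with or without it. If mood or age partly carry baseline cognition, the inflation would be smaller than shown.

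**Step 4: the opposite case.** Let each patient have a stable true level T, with baseline = T + e1 and post = T + e2. Neural change is related to T but not to cognitive change. The correlations with observed baseline are the same as in Step 2 (n = 52, 20,000 runs):

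| rho | Baseline with neural change (size) | Raw correlation with change | Baseline-adjusted alone |
|---|---|---|---|
| 0.7 | 0.3 | 4.9% | 14.8% |
| 0.7 | 0.4 | 4.8% | 25.4% |
| 0.5 | 0.3 | 4.9% | 24.7% |
| 0.5 | 0.4 | 4.9% | 42.7% |

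Here the raw correlation is valid and the adjusted test is the inflated one.

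**Step 5: require both.** The chance that both tests reject cannot exceed the smaller of the two. In Steps 2 and 3 that is the adjusted test, and in Step 4 the raw one, each at about 5%. Simulated joint rejection at n = 52 was 2.6 to 2.9% in Step 3 and 2.5 to 2.9% in a rerun of Step 4.

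**The case against.** The strongest objection is that Step 2 builds in its own answer. It treats the whole correlation between change and baseline as acting through the observed baseline score. Much of that correlation may be regression to the mean, and noise in the baseline score confounds only if it also drives neural change. Procedure puts the baseline scan on day 1 and the cognitive tests on day 2, 1 to 3 days apart, so shared test-day noise is not to be expected. Step 4 shows the consequence. This is the change-score versus baseline-adjustment problem (Lord's paradox) for a predictor that was not randomised, and the documents do not settle which model applies. This part stands. A reader might infer that adding the baseline composite restores 5% in every case, or that a baseline-adjusted partial correlation should replace the gate. Neither is supported.

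It also stands that the link from baseline cognition to neural change is not documented. Partial normalization is a hypothesis about direction, and room to move on the scan depends on baseline activity rather than on the composite. A reader might infer that the protocol itself names baseline cognition as the driver of gain under action-based cognitive remediation. It does not: its evidence is from EPO trials and concerns the chance of response to that treatment.

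Finally, the article does not say that the covariate list is complete, and it does not name the regression's dependent variable. I read that as change in the composite from the preceding sentence. These points soften the finding but do not remove it. The article commits to a specific adjustment set, which is more than silence left to a fuller document. Once baseline is in the model, change and final score give the same neural coefficient.

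**Conclusion.** The point holds in a limited form. The covariates named for the follow-up regression do not include the baseline composite. If baseline cognition is related to both composite change and early neural change, false positives at n = 52 are about 13 to 30% under assumed correlations of 0.39 to 0.5 and 0.3 to 0.4. If either link is absent, there is no inflation from this source.

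The documents do not support the stronger reading that a significant neural coefficient would merely restate baseline impairment. They show neither link for this treatment, and under the measurement-noise model the stated raw correlation is sound. The two-test rule was checked under these two data models, not under every mixture of them. The analysis is exploratory and conditional. The primary and secondary outcomes and the sample size are untouched; only the strength of a biomarker claim is affected.

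**What to change.** In the closing paragraph of Strategic picture encoding:

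1. Keep the raw correlation of early neural change with post-treatment change in the composite as the gate.
2. Add the baseline composite, and baseline activity in the same region, to the follow-up regression alongside mood and demographic characteristics.
3. Call early neural change predictive only if both the gate and the baseline-adjusted neural coefficient are significant.

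All values are already collected. The cost is a sentence or two of text, one or two degrees of freedom, and a somewhat lower chance of declaring a biomarker.

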### Sample size and power calculation

The power calculation was carried out by Pharma Consulting Group (Uppsala, Sweden) (http://www.pharmaconsultinggroup.com) using SAS, based on findings from a previous randomized controlled trial run by our group assessing the effect of 8 weeks of EPO treatment on the same cognitive composite score [50]. The difference between the EPO and saline-treated groups regarding changes on the cognitive composite score was 0.5 standard deviations (SD) from baseline. In this trial, a clinically relevant difference between the ABCR and the control groups following 10 weeks of treatment is assumed to be 0.4 SD (corresponding to a medium effect size) on the primary outcome, with a mean change in the cognitive composite score of 0.5 SD. The power calculation assumes normally distributed data and uses two-sided sample *t-*tests. With these assumptions, we will achieve a power of >80% to detect a clinically relevant difference between the treatment groups at an alpha level of 0.05 with 26 participants in both the ABCR and control groups, respectively. Assuming a 10% drop-out rate from baseline to treatment completion, we will recruit up to 58 participants to achieve complete data sets for 52 participants.

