**Methods/design:**

The trial has a randomized, controlled, parallel-group design. In total, 58 patients with BD in full or partial remission aged 18–55 years with objective cognitive impairment will be recruited. Participants are randomized to 10 weeks of ABCR or a control group. Assessments encompassing neuropsychological testing and mood ratings, and questionnaires on subjective cognitive complaints, psychosocial functioning, and quality of life are carried out at baseline, after 2 weeks of treatment, after the end of treatment, and at a six-month-follow-up after treatment completion. Functional magnetic resonance imaging scans are performed at baseline and 2 weeks into treatment. The primary outcome is a cognitive composite score spanning verbal memory, attention, and executive function. Two complete data sets for 52 patients will provide a power of 80% to detect a clinically relevant between-group difference on the primary outcome. Behavioral data will be analyzed using mixed models in SPSS while MRI data will be analyzed with the FMRIB Expert Analysis Tool (FEAT). Early treatment-related changes in neural activity from baseline to week 2 will be investigated for the dorsal prefrontal cortex and hippocampus as the regions of interest and with an exploratory whole-brain analysis.

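### The stated power of over 80% with 26 per arm does not fit a medium effect of 0.4 SD; it reproduces only if the 0.5 printed as a mean change is the SD of the change score

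*Protocol article*

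**What the plan says.** The section on sample size and power calculation in the protocol article bases the calculation on an earlier trial by the same group, in which the arms differed by 0.5 SD in change on the same composite. For the present trial the difference between arms is "assumed to be 0.4 SD (corresponding to a medium effect size) on the primary outcome, with a mean change"; the closing clause reads in full "with a mean change in the cognitive composite score of 0.5 SD". On the method, "The power calculation assumes normally distributed data and uses two-sided sample" t-tests. The conclusion is that "we will achieve a power of >80% to detect a clinically relevant difference between the treatment groups", and this is claimed "at an alpha level of 0.05 with 26 participants in both the ABCR and control groups, respectively". Allowing for 10% drop-out, 58 are recruited to obtain 52 complete data sets.

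The abstract repeats the claim without an effect size: "Two complete data sets for 52 patients will provide a power of 80% to detect a clinically relevant between-group difference on the primary outcome".

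The section on outcome assessments defines the primary outcome as the mean of six z-transformed test scores.

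**The concern.** A two-sample t-test power calculation needs a difference, the SD of the quantity compared, the sample size and alpha. The section gives a difference of 0.4 SD, calls it medium, and adds a second figure, 0.5 SD, described as a mean change. A mean change does not enter this calculation. If it is set aside, the remaining inputs are a standardized difference of 0.4 with 26 per arm, which falls far short of 80% power.

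This paragraph is the only justification of the sample size for the primary hypothesis. Readers will use it to decide what size of benefit a non-significant result makes unlikely. A trial powered for 0.4 SDs of change and one powered for 0.8 SDs of change support very different readings of a null result, and the text does not settle which this is.

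**Working it through.** **Inputs** (sample size section): two-sided t-test, alpha 0.05, n = 26 per arm, difference 0.4, second figure 0.5, stated power above 80%, drop-out 10%.

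**Formula.** With standardized difference d, the test statistic follows a noncentral t distribution with 2n − 2 = 50 degrees of freedom and noncentrality d × √(n/2). The two-sided 5% critical value is 2.009.

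**Reproducing the plan's figure.** Take 0.4 as the difference and 0.5 as the SD of change in the same units:
- d = 0.4/0.5 = 0.8
- noncentrality = 0.8 × √13 = 2.88
- power = 80.7% with 26 per arm and 79.1% with 25, so 26 is the smallest sufficient number
- recruitment = 52/0.9 = 57.8, rounded up to 58

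All three printed figures (above 80%, 26 and 58) are recovered.

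**Taking 0.4 as the standardized difference**, as the medium label suggests:
- noncentrality = 0.4 × √13 = 1.44
- power = 29.3%, about 51 points below 80%
- 80% power would need 100 per arm

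A one-sided test (41.2%) does not close the gap, nor does counting all 58 recruits, 29 per arm (32.2%).

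**Smallest standardized difference with 80% power at 26 per arm:** 0.79.

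**How the units matter (assumptions only).** If 0.4 is in raw composite units, power depends on the composite's cross-sectional SD and on the baseline to follow-up correlation r. The document gives neither. If each of the six z-scores has unit variance and they share a common correlation ρ, the composite SD is √((1 + 5ρ)/6). With equal variances at both visits, the SD of change is composite SD × √(2(1 − r)). With 26 per arm and a t-test on change scores:

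| Assumed composite SD | 0.4 in composite SDs | r needed for SD of change 0.5 | Power at r = 0.7 | Power at r = 0.8 |
|---|---|---|---|---|
| 1.00 (rescaled to unit SD, or ρ = 1) | 0.40 | 0.875 | 45% | 61% |
| 0.76 (ρ = 0.5) | 0.52 | 0.79 | 67% | 83% |
| 0.71 (ρ = 0.4) | 0.57 | 0.75 | 73% | 89% |
| 0.65 (ρ = 0.3) | 0.62 | 0.70 | 81% | 93% |

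The range runs from 45% to 93%, so no single figure from this table can be attributed to the trial.

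**The case against.** The strongest reply is that the calculation itself is sound. The 0.5 stands in the same sentence as the 0.4, and dividing one by the other returns the stated power, the exact minimum per arm and the recruitment target. That is unlikely to be coincidence, so the fault may be one misnamed parameter. This stands, and it rules out saying that the power figure has been shown to be wrong.

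A second reply is that medium may be defensible. An average of six imperfectly correlated z-scores has an SD below 1, so 0.4 composite units could be 0.52 to 0.62 cross-sectional SDs (ρ from 0.5 to 0.3) and still be 0.8 SDs of change. This also stands as a possibility. The document does not say that this is meant, so the label needs a stated SD rather than automatic deletion.

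Stronger readings are tempting, and the document does not support them:
- **That the trial would miss its target benefit about 7 times in 10.** This holds only if 0.4 is the standardized effect. If 0.5 is the SD of change, a difference of 0.4 units is missed about 2 times in 10.
- **That it is underpowered for the earlier trial's 0.5 SD effect.** A standardized 0.5 gives 42% power, but 0.5 units with an SD of change of 0.5 gives d = 1.0 and 94%. The scale of that earlier figure is not given.
- **That the calculation requires a correlation of 0.875.** This assumes a composite with unit SD.
- **That the abstract is wrong.** It names neither 0.4 nor medium, and is correct if 0.5 is the SD of change.

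**Conclusion.** The point holds as an inconsistency between the stated power and the effect it is stated for. A standardized difference of 0.4 and power above 80% with 26 per arm cannot both be true: the power is 29.3%. The printed figures agree with each other only at a standardized difference of 0.8, which requires the 0.5 to be the SD of change. That reading fits exactly, but it is an inference, because the text calls the 0.5 a mean change and leaves the units of the 0.4 undefined.

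A shortfall in power is not established. What is established is that 26 per arm gives 80% power only for a difference of about 0.79 SDs of the quantity tested, and that the paragraph does not tell the reader so. These results assume the plan's own two-sample t-test with complete data on 26 per arm. Any gain from baseline adjustment or repeated measures in the mixed model is outside the stated calculation.

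**What to change.** Restate the sample size paragraph without changing the number of participants. Suggested content: with 26 per arm and a two-sided t-test at alpha 0.05, power is 81% for a difference of 0.4 composite units if the SD of the change score is 0.5 in the same units, a standardized difference of 0.8. Give the source of the 0.5, and delete the description of it as a mean change. Remove the medium label, or state the SD to which it refers.

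If the original calculation shows that 0.4 was meant as the standardized effect, report the power as 29% instead; the abstract's 80% would then have to change too. Otherwise the abstract can stay as it is. Any power figure that depends on a baseline to follow-up correlation should be labelled as an assumption and given with the composite SD used.

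The cost is a check of the original calculation and the rewording of one paragraph. No additional patients are needed to make this correction.
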